## **10 Selection and withdrawal of participants**

### **10.1 Inclusion Criteria**

A patient will be eligible for inclusion in this trial only if all of the following criteria apply:

1. Male or female patients between 50 and 85 years of age inclusive at screening, with a body weight  $\geq 45$  kg and BMI  $\leq 35$  kg/m^2.
2. Patients with a clinical diagnosis of COPD with GOLD Stages 1, 2, 3 or 4, or GOLD-U. Gold U are patients with a clinical history consistent with COPD and a reduced FEV1 but a preserved (i.e.  $>0.7$ ) FEV1/VC ratio in the absence of an alternative diagnosis. For the purpose of EVOLUTION, establishing an absence of an alternative diagnosis will normally include as a minimum physical examination of the thoracic cage, a normal chest radiograph and the demonstration of a maximal sniff nasal inspiratory pressure  $>50$  cm H2O
3. Patient has FEV1/FVC  $< 0.7$  post-bronchodilator.
4. Patient is a smoker or an ex-smoker with a smoking history of at least 10 pack years (1 pack year = 20 cigarettes smoked per day for 1 year or equivalent).
5. Baseline fibrinogen value of  $>2.8$  g/L (Klauss method)
6. ALT  $< 2 \times$ ULN at screening; alkaline phosphatase and bilirubin  $\leq 1.5 \times$ ULN at screening (isolated bilirubin  $>1.5 \times$ ULN is acceptable if bilirubin is fractionated and direct bilirubin  $<35\%$ ).
7. Patients must have a QTc  $<450$  msec on screening (V1) ECG (using average value of triplicate ECGs). For patients with complete Right bundle branch block, the QTc must be  $<480$  msec on Screening V1 ECG. Patients with other ECG findings will be excluded if warranted at the discretion of the CI/PI. QTc readings will be QTcF.
8. (For the optional MRI sub-study (n/a if patient does not consent to MRI)): Patients who fulfil local imaging centre requirements will be enrolled.

### **10.2 Exclusion Criteria**

The presence of any of the following will preclude patient inclusion:

1. Inability in the opinion of the PI to provide Informed Consent.
2. A cardiovascular event in the last 6 months (i.e. acute coronary syndrome, unstable angina, CABG, PCI, stroke, MI, carotid endarterectomy).
3. Patients on daunorubicin, doxorubicin, topotecan, mitoxantrone.
4. Previous lung reduction surgery.
5. Patients with known clinically significant pulmonary diagnoses in which inflammation is thought to play a role including diagnosis of bronchiectasis, sarcoidosis, lung fibrosis, interstitial lung disease, or  $\alpha 1$ -antitrypsin deficiency.
6. A positive pre-trial Hepatitis B surface antigen or positive Hepatitis C antibody result within 3 months of screening.

7. Current or chronic history of liver disease, or known hepatic or biliary abnormalities (with the exception of Gilbert's syndrome or asymptomatic gallstones).
8. Patients with known chronic infections such as HIV or known active tuberculosis.
9. Patients with rheumatoid arthritis, connective tissue disorders and other conditions known to be associated with active chronic inflammation (e.g. Inflammatory Bowel Disease).
10. Insulin controlled Type 1 or Type 2 diabetics.
11. Diabetics on oral hypoglycaemics/diet with HbA1c (DCCT) > 8% (OR HbA1c (IFCC) > 64 mmol/mol), at screening. [note: fasting glucose to be checked again at first FDG-PET/CT scan, and if glucose > 11mmol/L at that visit, patients will be excluded from trial]
12. Participation in a previous research trial in the last 3 years which involved exposure to significant ionising radiation (i.e. cumulative research radiation dose >5 mSv)
13. History of malignancy within the past 5 years (with the exception of localized carcinoma of the skin that has been resected for cure).
14. Previous exposure to Losmapimod.
15. Patients who have donated more than 500 mL of blood within 2 months prior to the trial medication administration, Visit 3 (Day 1).
16. Participation in a clinical trial where the patient has received a drug or new chemical entity within 30 days or 5 half-lives, or twice the duration of the biological effect of the drug (whichever is longer) prior to the first dose of trial medication, Visit 3 (Day 1).
17. History of alcohol/drug abuse or dependence within 6 months of the trial, Screening Visit 1 (Day -45 to -14).
18. Women of childbearing potential are excluded from this trial. Women must be of non-childbearing potential [i.e. either postmenopausal or documented hysterectomy and/or bilateral oophorectomy – tubal ligation is not sufficient]. For the purposes of this trial, postmenopausal is defined as being amenorrhoeic for greater than 2 years with an appropriate clinical profile, e.g. age appropriate, history of vasomotor symptoms.  
  
An unwillingness of male patients to abstain from sexual intercourse with pregnant or lactating women; or an unwillingness of the patient to use a condom/spermicide in addition to having their female partner use another form of contraception such as an intrauterine device (IUD), diaphragm with spermicide, injectable progesterone, sub-dermal implants or a tubal ligation.
19. Any medical history or clinically relevant abnormality that is deemed by the principal investigator and/or medical monitor to make the patient ineligible for inclusion because of a safety concern.
20. Use of systemic corticosteroids (oral or IV) 4 weeks prior to Visit 2 (Day -14 to -1).

### **10.3 Method of Blinding**

The placebo tablets will be manufactured to appear identical to the Losmapimod tablets. Packaging and labelling at point of supply to the patient will be blinded against the active preparation. The site pharmacy will be unblinded. Further details regarding blinding are as described in the pharmacy section of the TPM.

Recall of IMP for any reason, including a manufacturing defect, will be managed by Cambridge Clinical Trials Unit.

## 10.4 Emergency Unblinding

To ensure 24 hour access the services of the local pharmacy department will be used: a pharmacist on call will be available through switchboard: CUH - [name] & RBH - [name].

The following questions will be asked of a physician prior to any unblinding taking place:

- Name (CI or PI or designated named person)
- Details of the AE or SAE
- Reason for needing the unblinding

Pharmacy will then follow the unblinding procedure as described in the pharmacy section of the TPM.

## 10.5 Participant Withdrawal Criteria and Stopping Criteria

Reasons for participant withdrawal will be recorded in the electronic Case Report Form (eCRF). Primary reasons for withdrawal may include: SUSAR, adverse event, withdrawal of consent, lost to follow-up, protocol deviation, participant non compliance, lack of efficacy, participant reached protocol-defined stopping criteria or trial closed/terminated. All the above are at the discretion of CI/PI.

In addition participants must be  $\geq 70\%$  to  $\leq 100\%$  compliant on taking trial medication between each on-treatment visits. Participants who fall outside this range should be re-educated on treatment compliance. In assessing compliance, it should be noted that participants may discontinue their use of trial drug due to an exacerbation. See section 10.5.3 for further information concerning participants' withdrawal due to exacerbation.

Specific withdrawal criteria relating to biochemistry, ECG abnormalities and exacerbation of COPD are listed below. Participants who are withdrawn from the trial will be replaced at the discretion of the CI/PI.

### 10.5.1 Biochemistry

Liver chemistry threshold stopping criteria have been designed to assure subject safety and to evaluate liver event aetiology (in alignment with the US Food and Drug Administration premarketing clinical liver safety guidance).

IMP will be stopped for a participant if any of the following liver chemistry stopping criteria is met:

1. ALT  $\geq 3 \times \text{ULN}$  and total bilirubin  $\geq 2 \times \text{ULN}$  ( $>35\%$  direct bilirubin\*);  
\*serum bilirubin fractionation should be performed if testing is available; if unavailable, withdraw subject (if ALT  $\geq 3 \times \text{ULN}$  and total bilirubin  $\geq 2 \times \text{ULN}$ ) and measure urinary bilirubin via dipstick.
2. ALT  $\geq 5 \times \text{ULN}$ .
3. ALT  $\geq 3 \times \text{ULN}$  if associated with symptoms (new or worsening) believed to be related to hepatitis (such as fatigue, nausea, vomiting, right upper quadrant pain or tenderness or jaundice) or hypersensitivity (such as fever, rash or eosinophilia).
4. ALT  $\geq 3 \times \text{ULN}$  persists for  $\geq 4$  weeks.
5. ALT  $\geq 3 \times \text{ULN}$  and cannot be monitored weekly for 4 weeks.

6. Participants with ALT  $\geq 3 \times \text{ULN}$  **and**  $< 5 \times \text{ULN}$  **and** bilirubin  $< 2 \times \text{ULN}$ , who do not exhibit hepatitis symptoms or rash, can continue IMP as long as they can be monitored weekly for 4 weeks. See Section 14. Details on weekly follow-up procedures for these participants.

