### **14.1.1 Safety Follow-Up Procedures for participants with ALT $\geq$ 3xULN and bilirubin $\geq$ 2xULN (>35% direct)**

This event is considered an SAE (see Section 13.1.2). Serum bilirubin fractionation should be performed if testing is available. If fractionation is unavailable, urinary

bilirubin is to be measured via dipstick (a measurement of direct bilirubin, which would suggest liver injury).

- Make every reasonable attempt to have the participants return to the clinic (within 24 hours) for repeat liver chemistries, additional testing and to be monitored closely (with specialist or hepatology consultation recommended).
- Monitor participants twice weekly until liver chemistries (ALT, AST, alkaline phosphatase, bilirubin) resolve, stabilize or return to within baseline values.

**14.1.2 Safety Follow-Up Procedures for participants with ALT  $\geq$  5xULN or ALT  $\geq$  3xULN who have hepatitis symptoms or rash, can't be monitored for 4 weeks or have elevations that persist  $\geq$  4 weeks [Stopping Criteria section 10.5]:**

- Make every reasonable attempt to have the subject return to the clinic within 24-72 hours for repeat liver chemistries and additional testing.
- Monitor participants weekly until liver chemistries (ALT, AST, alkaline phosphatase, bilirubin) resolve, stabilize or return to within baseline values.

**14.1.3 Safety Follow-Up Procedures for participants with ALT  $\geq$  3xULN and  $<$  5xULN and bilirubin  $<$  2xULN, who do not exhibit hepatitis symptoms or rash:**

- Notify the medical monitor within 24 hours of learning of the abnormality to discuss participant safety.
- Participant can continue IMP if liver chemistries (ALT, AST, alkaline phosphatase, bilirubin) can be monitored weekly for up to 4 weeks.
- If at any point these participants meet the liver chemistry stopping criteria (outlined in Section 10.5), immediately withdraw IMP, perform additional testing and continue safety follow-up until liver chemistries resolve, stabilize or return to baseline values.
- After 4 weeks of monitoring, if ALT  $<$  3xULN and bilirubin  $<$  2xULN, participants must be monitored twice monthly until liver chemistries normalize or return to within baseline values.

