**14.1.4 Recommended additional Follow-Up Procedures for participants who meet *any* of the stopping criteria:**

- Viral hepatitis serology including:
  - Hepatitis A IgM antibody;
  - Hepatitis B surface antigen and Hepatitis B Core Antibody (IgM);
  - Hepatitis C RNA;
  - Cytomegalovirus IgM antibody;
  - Epstein-Barr viral capsid antigen IgM antibody (or if unavailable, obtain heterophile antibody or monospot testing);
  - Hepatitis E IgM antibody.
- record the time of the last dose
- Serum creatine phosphokinase (CPK) and lactate dehydrogenase (LDH).
- Fractionated bilirubin, if total bilirubin  $\geq$  2xULN.
- Assess eosinophilia

- Record the appearance or worsening of clinical symptoms of hepatitis (fatigue, nausea, vomiting, right upper quadrant pain or tenderness, fever, rash or eosinophilia) as relevant on the AE CRF
- Record use of concomitant medications, paracetamol, herbal remedies, other over the counter medications, or putative hepatotoxins on the Concomitant Medications CRF.
- Record alcohol use on the Liver Events eCRF.

The following are required for participants with ALT  $\geq$  3xULN **and** bilirubin  $\geq$  2xULN (>35% direct) but are optional for other abnormal liver chemistries:

- Anti-nuclear antibody, anti-smooth muscle antibody, Type 1 anti-liver kidney microsomal antibodies and quantitative total immunoglobulin G (IgG or gamma globulins).
- Serum paracetamol adduct HPLC assay (quantifies potential paracetamol contribution to liver injury in participants with definite or likely paracetamol use in the preceding week).
- Liver imaging (ultrasound, magnetic resonance, or computerized tomography) to evaluate liver disease.
- The Liver Imaging and/or Liver Biopsy eCRFs are also to be completed if these tests are performed.

The procedures listed below are to be followed if a subject has ALT, bilirubin and/or INR elevations that meet the definition of an SAE (as defined in Section 13.1.2):

- Notify the medical monitor within 24 hours of learning of the abnormality to confirm follow-up.
- Complete the liver event eCRFs.
- Upon completion of the safety follow-up withdraw the subject from the trial unless further safety follow up is required.
- Make every reasonable attempt to have participants return to the clinic within 24 hours for repeat liver chemistries, additional testing, and close monitoring (with specialist or hepatology consultation recommended).

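### The symptom lists that decide between stopping and continuing IMP after an ALT rise do not match across Sections 10.5.1 and 14, so one narrow group fits both the stopping rule and the permission to continue

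*Protocol*

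**What the plan says.** Protocol Section 10.5.1 opens its numbered list with a mandatory instruction: "IMP will be stopped for a participant if any of the following liver chemistry stopping criteria is met".

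- **Criterion 3** applies at ALT of 3xULN or more with new or worsening symptoms believed related to one of two groups. The first is hepatitis (fatigue, nausea, vomiting, right upper quadrant pain or tenderness, jaundice). The second is "or hypersensitivity (such as fever, rash or eosinophilia").
- **Item 6** is numbered in the same list but permits continuation. It covers ALT from 3 to below 5xULN with bilirubin below 2xULN in participants "who do not exhibit hepatitis symptoms or rash, can continue IMP as long as they can be monitored weekly for 4 weeks". It then refers to Section 14 for "Details on weekly follow-up procedures for these participants".

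Section 14 takes up the same participants in three places.

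- **14.1.2**, by its heading, covers ALT of 5xULN or more, and ALT of 3xULN or more with hepatitis symptoms or rash, with monitoring not possible, or with persistence of 4 weeks or more. It ends with a cross-reference to the Section 10.5 stopping criteria and asks for a return to clinic within 24-72 hours.
- **14.1.3**, by its heading, covers the item 6 group, again excluding only hepatitis symptoms or rash. Its second bullet reads "Participant can continue IMP if liver chemistries (ALT, AST, alkaline phosphatase, bilirubin) can be monitored weekly for up to 4 weeks". Its third bullet begins "If at any point these participants meet the liver chemistry stopping criteria (outlined in Section 10.5), immediately withdraw IMP".
- **14.1.4**, for participants who meet any stopping criterion, says: "Record the appearance or worsening of clinical symptoms of hepatitis (fatigue, nausea, vomiting, right upper quadrant pain or tenderness, fever, rash or eosinophilia").

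**The concern.** A rule that stops treatment and a rule that lets it continue should exclude each other. Here they are meant to be complementary, but they are built on different lists. Criterion 3 has two limbs, hepatitis and hypersensitivity. Item 6 carries over the first limb and only one of the three hypersensitivity examples. Fever and eosinophilia drop out, and the headings of 14.1.2 and 14.1.3 repeat the shortened wording.

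At stake is a participant-safety decision on an unlicensed drug. Section 14 says that the manufacturer wants all sentinel events of liver dysfunction recorded. Someone at either of the two sites who consults only 10.5.1 would find a stop and a permission that fit the same participant, with no statement there of which prevails. The signs are ones the trial will see: eosinophils are in the haematology panel (Section 12.2), and Section 11.2.2 reports pyrexia more often on Losmapimod than on placebo. That section adds that most of those cases came from two 28-day neuropathic pain studies and that many accompanied mild illnesses.

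The point does not touch endpoints, sample size or analysis.

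**Working it through.** No sample size or power figure is involved, so the check is mainly a comparison of passages.

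**1. The lists side by side**

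| Place | Effect | Hepatitis symptoms | Rash | Fever | Eosinophilia |
|---|---|---|---|---|---|
| 10.5.1, criterion 3 | stop | yes, including jaundice | yes | yes | yes |
| 10.5.1, item 6 | may continue if absent | yes, not itemised | yes | not named | not named |
| 14.1.2 heading | stopped group, return in 24-72 h | yes, not itemised | yes | not named | not named |
| 14.1.3 heading | may continue if absent | yes, not itemised | yes | not named | not named |
| 14.1.4 | recording, after a stopping criterion is met | yes, without jaundice | yes, as hepatitis | yes, as hepatitis | yes, as hepatitis |

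**2. Which profiles meet both a stopping criterion (1 to 5) and item 6?** I crossed three ALT bands (below 3, 3 to below 5, and 5xULN or more) with six yes/no factors: bilirubin at least 2xULN, hepatitis symptoms, rash, fever or eosinophilia believed to be hypersensitivity, weekly monitoring possible, and persistence of 4 weeks or more. That gives 3 x 2^6 = 192 combinations.

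- *Hepatitis symptoms read as in criterion 3:* three combinations meet both. All have ALT from 3 to below 5xULN, bilirubin below 2xULN, no hepatitis symptoms, no rash, and weekly monitoring possible. They differ in the last two factors: fever or eosinophilia alone, persistence alone, or both.
- *Hepatitis symptoms read as in 14.1.4:* only persistence alone remains.

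The overlap through persistence alone is not a real conflict, because the permission is limited to 4 weeks of monitoring. What is left is the profile with fever or eosinophilia, and only under the first reading.

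**3. Which reading fits item 6?** If item 6 used the 14.1.4 meaning, naming rash separately would be redundant, because 14.1.4 already counts rash as a hepatitis symptom. Naming it fits the two-limb split of criterion 3. The 14.1.4 list is also a recording instruction for participants who have already met a stopping criterion, not a definition for 10.5.1. Neither list contains the other: 14.1.4 omits jaundice, and the hepatitis limb of criterion 3 omits fever, rash and eosinophilia.

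**4. Does the protocol settle the overlap?** On IMP, yes, when read whole: the third bullet of 14.1.3 gives precedence to the Section 10.5 stopping criteria. On follow-up, not clearly. By heading, the participant belongs to 14.1.3, which sets no 24-72 hour return. By its cross-reference to Section 10.5, 14.1.2 could claim the same participant.

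**5. How many participants?** Inputs: ALT of 3xULN or more in 0.9% on Losmapimod and 0.5% on placebo in earlier studies (Section 11.2.2), and about 30 per arm (Section 16.4).

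- Expected number = 30 x 0.009 + 30 x 0.005 = 0.27 + 0.15 = 0.42.
- Chance of at least one = 1 - 0.991^30 x 0.995^30 = 0.34.

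These figures count everyone with ALT of 3xULN or more. The group with ALT below 5xULN, bilirubin below 2xULN and only fever or eosinophilia is smaller; the protocol gives no figure for it.

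**The case against.** The strongest defence is that Section 14 resolves the matter. Item 6 sends the reader there, and 14.1.3 withdraws IMP at once when a Section 10.5 stopping criterion is met. The stop is mandatory and the permission is only permissive, so these are not two commands of equal force. That stands, and it defeats the reading that a colleague might infer: that the protocol orders the same participant both to stop and to continue, or lets dosing go on after a stopping criterion is met. Item 6 does not expressly permit continuation with fever or eosinophilia either; it reaches them only by leaving them out.

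Other parts of the defence also stand. Criterion 3 requires symptoms believed related to hepatitis or hypersensitivity, so a fever from an intercurrent infection need not count. Item 6 needs bilirubin below 2xULN and feasible weekly monitoring. Section 14.1.3 requires contact with the medical monitor within 24 hours, which gives both sites a common check. The wording of item 6 is plainly a permission, so its place in the list is largely editorial.

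What the defence does not remove is the mismatch. The precedence rule is not in 10.5.1, where the stopping decision is set out. It sits in the third bullet of a subsection whose heading admits this participant and whose second bullet allows continuation. It points back to the Section 10.5 list, which as numbered includes item 6. The appeal to 14.1.4 as a cure fails for the reasons in the working, and the defence leaves the choice between 14.1.2 and 14.1.3 open.

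**Conclusion.** The point holds as an inconsistency of wording in a participant-safety rule. Criterion 3, item 6, the headings of 14.1.2 and 14.1.3, and the list in 14.1.4 do not agree on which signs count. One profile meets both the stop and the permission: ALT from 3 to below 5xULN, bilirubin below 2xULN, weekly monitoring possible, and fever or eosinophilia believed to be hypersensitivity as the only sign. The protocol as a whole points to stopping; 10.5.1 alone does not say so, and the follow-up subsection for this participant is uncertain.

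The practical size is small. About 0.4 participants with ALT of 3xULN or more are expected in the trial, and fewer in the affected group. This assumes that rates from earlier studies in other populations carry over and that about 30 per arm are exposed. The exposed number may be higher, since Section 10.5 allows withdrawn participants to be replaced. Rarity lowers the priority but does not remove the point, because a stopping rule has to be clear when a rare event occurs. I rate it a minor-to-moderate safety wording correction. No view is taken on which clinical rule is right.

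**What to change.** The sponsor and medical monitor should reconcile these passages:

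1. Decide which symptoms and signs govern, and use one identical list in 10.5.1 criterion 3 and item 6, the headings of 14.1.2 and 14.1.3, and 14.1.4 (including its repeat later in that section), so that stopping and continuing exclude each other.
2. Move item 6 out of the numbered stopping list into its own paragraph.
3. State the precedence rule of 14.1.3 beside that paragraph, so that 10.5.1 can be read on its own.
4. Make clear whether 14.1.2 or 14.1.3 applies to a participant who meets criterion 3 through hypersensitivity signs alone.

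The cost is a protocol wording amendment and a note to the two sites. It needs no extra tests or visits and does not change the analysis.

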### 10.5.2 ECG

Participant that meets the criteria below will be withdrawn from the trial. The QT correction formula used to determine discontinuation should be the same one used throughout the trial.

For participants with underlying bundle branch block, follow the criteria listed below:

**Table 1:**

| Baseline QTc with bundle branch block | Discontinuation QTc with bundle branch block |
|---------------------------------------|----------------------------------------------|
| $< 450 \text{ msec}$                  | $> 500 \text{ msec}$                         |
| $450 - < 480 \text{ msec}$            | $\geq 530 \text{ msec}$                      |

Change from baseline: QTc  $> 60 \text{ msec}^*$

\*Withdrawal decisions are to be based on an average QTc value of triplicate ECGs. If an ECG demonstrates a prolonged QT interval, obtain 2 more ECGs over a brief period, and then use the averaged QTc values of the 3 ECGs to determine whether the subject should be discontinued from the trial.

